### Intervention

The BM-MA consists of audio guides of BM practices derived from mindfulness exercises available in the MBSR and mindfulness-based cognitive therapy (MBCT), an intervention adapted from the MBSR for preventing relapse in major depression. Examples of mindfulness practices that are included in the BM-MA are mindfulness of breathing, mindfulness of sounds, body scan meditation, mindful stretching, mountain meditation, and loving-kindness meditation. The audio guides for these mindfulness practices were developed (in the Indonesian language) by qualified MBCT teachers based in Indonesia and professionally recorded in an authorized recording studio. Each audio guide lasts between 5 and 20 minutes, and participants will be expected to engage in 10-20 minutes of mindfulness practice in total daily.

A progression of mindfulness practices was recommended to the participants in the first 10 days of practice, beginning with brief, introductory mindfulness exercises (eg, mindfulness of breathing), followed by practices that are lengthier and more open ended in nature (eg, mountain meditation, choice-less awareness meditation). After the first 10 days of practice, the participants were allowed to daily engage in any practice tracks that they like. The app also contains a feature that allows participants to track the overall duration and frequency of practice over a period of 21 days. Prior to downloading the app, the participants received an orientation to mindfulness practice by a trained mindfulness teacher via a Zoom meeting, and the session consisted of an introduction to the practice of mindfulness, stigma related to mental health, common myths about mindfulness practice, setting up a suitable environment for mindfulness practice, and troubleshooting potential difficulties that may arise during mindfulness practice (eg, dealing with difficult thoughts and emotions). The orientation session served the purpose of establishing a common level of mindfulness knowledge among the participants and ensuring their comprehension of how to use the BM-MA. They were asked to set aside time daily to commit to home mindfulness exercises using the app.

### Recruitment and Sample Size

This study’s sample comprised Indonesian high school teachers. The sample was drawn from 2 public senior high schools after a request for volunteers was sent over email by local government partners. Individuals who answered within 1 week were directed to a webpage on Qualtrics that describes the study and screening process. In addition, recruiting advertisements based on the opinion of the school principals were distributed via the schools’ social media. Individuals who passed the screening process were included in the participant pool.

The inclusion criteria for the feasibility study were Indonesian certified senior high school teachers (1) who are aged 18 years and older, (2) can read and write in Indonesian, (3) have access to a smartphone, and (3) have a total Generalized Anxiety Disorder-7 (GAD-7) score of no more than 14 and a total General Health Questionnaire-12 (GHQ-12) score of no more than 20. The exclusion criteria for the feasibility study were (1) regular practice of mindfulness meditation (eg, 15-20 minutes per day, 2-3 times per week), (2) a history of ongoing and present treatment for a mental disorder, (3) a positive response to GHQ-12 questions regarding suicidal ideation, and (4) refusal to provide written informed consent. These criteria were designated to recruit participants without prior regular experience in mindfulness practice and with no severe symptoms of depression and anxiety. The criteria also contributed to a more homogenous selection of participants across conditions.

Random sampling was used in the 2 public senior high schools in Indonesia, with the unit that was randomized being the senior high schools themselves. The sample size for this feasibility study was 30 participants for each study arm, with 95% CIs and small standardized effect sizes [27].

### Acceptability and Feasibility

A mixed methodological study was used to evaluate the BM-MA’s feasibility and acceptability. Acceptability is defined as the extent to which an app is suitable [28], and is assessed by analyzing participants’ qualitative responses to structured interviews. The quantitative scale used to measure feasibility was the Client Satisfaction Questionnaire-8 (CSQ-8) [28]. Each item in the CSQ-8 is rated on a scale of 1-4, and total scores range from 8 to 32. More than 70% of participants must receive a score of 24 or above on the CSQ-8 [28], given a 10% acceptable error rate [29], and participate in structured qualitative interviews for acceptance to be determined.

Feasibility is defined by Feeley et al [30] as the ease of deployment of an app among adults. In this study, on the basis of app scores, feasibility will be evaluated descriptively by examining the ease of recruitment, enrollment rate, and attrition rate. Participants will also be required to complete an in-person final evaluation. End-of-line evaluations will involve the viability and acceptance of the mobile app, as well as structures qualitative interviews.

### Randomization and Blinding

Participants from 2 public senior high schools were randomly assigned to the BM-MA group or the CG in a 1:1 ratio. The app arbitrarily selected a block size (2, 4, or 6) and assigned a random order within the block. For example, we randomly allocated 30 participants to each group in this scenario. The BM-MA group was denoted as “M” and the CG as “C.” The possible groupings were MCCM, MMCMCC, CM, MC, and CMCM. As part of the screening consent procedure, participants were informed that this will be an interventional study in which they might be randomized to a variety of BM-MA groups.

The prior online mindfulness intervention revealed a substantial potential for attrition. To proactively address this problem, we identified all potential avenues for recruiting and factored in the attrition rate when determining the appropriate sample size [27,30]. Considering the features and design of this pilot project, it would not be possible to blind the treatment assignment and result evaluation. However, participants were provided with information regarding the significance of a 2-arm study design following the CONSORT checklist (can be seen in Multimedia Appendix 1) and were strongly advised against disclosing their group allocation to their coworkers. Although there may be possible problems, this strong methodology will guarantee that the BM-MA intervention is carried out with a high level of academic excellence.

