**Methods:**

We followed the SPIRIT (Standard Protocol Items: Recommendations for Interventional Trials) 2013 statement for this feasibility randomized controlled trial (RCT) protocol. A total of 60 Indonesian senior high school teachers were recruited for this study and randomly assigned to either the intervention group (BM-MA) or a wait-list control group (CG) in a 1:1 ratio. The BM-MA group was required to engage in mindfulness practices using the app for 10-20 minutes per day for 3 weeks. All participants were assessed with a battery of self-report measures at baseline, postintervention, and at 1-month follow-up. Validated scales used to measure the outcome variables of interest included the Satisfaction With Life Scale (SLS), the Teachers’ Sense of Efficacy Scale (TSES), the Self-Compassion Scale—Short Form (SCS-SF), Generalized Anxiety Disorder-7 (GAD-7), General Health Questionnaire-12 (GHQ-12), and the Five Facet Mindfulness Questionnaire (FFMQ). The practicality and acceptability of the app will be evaluated using the Client Satisfaction Questionnaire-8 (CSQ-8) and structured qualitative interviews. Data from the interviews will be analyzed with the deductive thematic analysis framework as a process of qualitative inquiry. Repeated measures ANOVA with groups (intervention vs control) as a between-subject factor and time as a within-subject factor (baseline, postintervention, and 1-month follow-up) will be used to examine the effects of the BM-MA on the outcome variables. The data will be analyzed using an intent-to-treat approach and published in accordance with CONSORT (Consolidated Standards of Reporting Trials) recommendations.

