## Methods

### Overview of Study Design

This feasibility study will use a repeated-measures, between-group RCT design and adhere to the CONSORT (Consolidated Standards of Reporting Trials) statement (Multimedia Appendix 1). The feasibility protocol presented followed the SPIRIT (Standard Protocol Items: Recommendations for Interventional Trials) 2013 statement (Multimedia Appendix 2) [26]. As determined by an initial screening instrument, participants were only recruited if they exhibited good overall health, had no past experience with mindfulness practice, and had not recently experienced any adverse life events. Individuals who matched the inclusion criteria (explained further in the subsequent section) and responded within the recommended time frame of 2 weeks were routed to a webpage and a participant information sheet via the Qualtrics platform. Participants from 2 public senior high schools were informed that they would be randomly assigned to a treatment group or a wait-list control group (CG) and were asked to provide written informed consent (see Multimedia Appendix 3) prior to completing a brief demographic questionnaire. The participants were subsequently randomly assigned to either the BM-MA group or the CG. Participants in the CG were notified that they were on a waiting list and were asked to answer questionnaires at baseline, postintervention, and at 1-month follow-up before being allowed access to the BM-MA intervention for an additional 21 days (if they wished to use it).

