### Data Analyses

The sociodemographic characteristics of the participants (eg, age) will be analyzed descriptively. Missing data, including participants who dropped out, will be treated using the intention-to-treat principle with multiple imputations of missing values [42]. Intention-to-treat analysis is a statistical method used in prospective randomized studies. It involves including all individuals who were randomly assigned to a group, regardless of whether they received any sort of treatment. These participants are then examined on the basis of their initial group assignment. This methodology enables the researcher to derive precise and impartial judgments regarding the efficacy of an intervention. This approach maintains the advantages of randomization, which cannot be presumed when using alternative methods of analysis.

The data will be examined using repeated-measures ANOVA with groups (BM-MA vs control) and 3 time periods as factors (baseline, day 21, day 41). In addition, Pearson correlation analysis will be undertaken to determine whether the subjective ratings of involvement and experience with the BM-MA by participants correlate with any potential improvements in well-being experienced by the BM-MA group. The variation in findings between the 2 groups will be encompassed by the 95% CI range for the significance of the effect. The amount of effect (Cohen d) will be calculated by dividing the median variation (from baseline, monitoring, and end line to follow-up) obtained from the results of the linear mixed model by the pooled SD at baseline.

Transcription will be conducted for all records of structured qualitative interviews. The qualitative data will undergo deductive theme analysis using a framework and will be used to create an initial codebook. The qualitative data will be analyzed using an iterative method by 2 coders, who will independently code all transcripts and then discuss any inconsistencies until consensus is established. The resulting comprehensive codebook will be input into qualitative analysis software.

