## Results

This protocol funding started in May 2023. Participants for this pilot RCT were recruited in December 2023, and the RCT was conducted from January through March 2024. Data analysis was conducted from March through May 2024. Paper writing based on the data analysis is ongoing. The expected results of this study will be published in December 2024. The BM-MA display can be seen in Figures 1-3.

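### School is controlled in neither the described allocation nor the planned analysis, and the unit of randomisation must be settled first; if teachers were allocated individually, the loss is modest chance error that can be removed cheaply

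*Protocol article*

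**What the plan says.** All references are to the protocol article.

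- **Randomization and Blinding** gives the allocation in working detail: "Participants from 2 public senior high schools were randomly assigned to the BM-MA group or the CG in a 1:1 ratio", and "The app arbitrarily selected a block size (2, 4, or 6) and assigned a random order within the block". It also prints sample blocks and the 30-per-group target. No stratification factor is named.
- **Overview of Study Design** also puts allocation at the level of the teacher, after consent and a demographic questionnaire: "The participants were subsequently randomly assigned to either the BM-MA group or the CG". No calendar date for randomisation is given.
- **Recruitment and Sample Size** says otherwise. It describes random sampling in the two schools, "with the unit that was randomized being the senior high schools themselves".
- **Data Analyses** names the model: "The data will be examined using repeated-measures ANOVA with groups (BM-MA vs control) and 3 time periods as factors". School does not appear.
- **Results** gives the timing: "Participants for this pilot RCT were recruited in December 2023, and the RCT was conducted from January through March 2024".

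**The concern.** The introduction attributes teachers' stress partly to workload, work routine and the workplace, which colleagues in a school share. School is therefore a plausible prognostic factor on the article's own account. It has only two levels and was known for every teacher before the trial period began.

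Two things are at stake.

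1. The article gives two different units of randomisation. If whole schools were allocated, one to each arm, any difference between the schools would be inseparable from the effect of the app.
2. If teachers were allocated individually without regard to school, the arms can differ by chance in school mix. A model with group and time alone leaves that difference in the estimate. Allocating within school, or fitting school in the model, removes most of it with no extra participants.

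**Working it through.** **Step 1. The unit of randomisation.** A block of 4 or 6 needs four or six units to fill it. Two schools could fill only one block of 2. The printed block patterns, the 1:1 ratio and 30 allocated to each group therefore fit individual allocation. They do not fit allocation of two schools. The sentence naming schools as the unit may be a misplaced remark about how the schools were sampled, but it does not say so. Read literally, with one school per arm, there is no replication of school within arm. No adjustment could then separate school from treatment, and stratifying by school would be impossible.

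The rest assumes individual allocation.

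**Step 2. Inputs.**
- From the article: 60 teachers, 30 per arm (30 + 30 = 60, which agrees with 1:1), two schools, block sizes 2, 4 or 6.
- Assumed, because the article does not give them: the school split (30:30, 20:40 or 15:45), a random order of entry by school, equal chance of each block size, and a school gap in outcome of 0.2 to 0.5 SD.

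The article gives no figure for school imbalance, so there is none to reproduce.

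**Step 3. Imbalance in school mix from one unstratified list.** Let *p* be the share of teachers from one school. With 30 per arm, the SD of the between-arm difference in that share is √[*p*(1−*p*) × (1/30 + 1/30) × 60/59].
- 30:30: √(0.25 × 0.0667 × 1.017) = 0.130
- 20:40: √(0.222 × 0.0667 × 1.017) = 0.123
- 15:45: √(0.1875 × 0.0667 × 1.017) = 0.113

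Simulating the stated blocks gives the same SDs and these tail figures:

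| School split | Difference of 20 points or more | Exact hypergeometric, arms fixed at 30 v 30 | Largest difference if blocks run within school |
|---|---|---|---|
| 30:30 | 18% | 19.6% | 7 points |
| 20:40 | 15–16% | 17.0% | 7 points |
| 15:45 | 7–8% | 7.2% | 10 points |

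The 95th percentile of the difference is about 23 to 27 points. Within-school blocks reduce its SD to 0.020–0.028, and no simulated difference reached 20 points.

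**Step 4. What that does to the estimate.** The shift in the group difference is the school-mix difference times the school gap.
- At 20 points: 0.20 × 0.2 = 0.04 SD to 0.20 × 0.5 = 0.10 SD.
- At the 95th percentile: about 0.05 SD for a gap of 0.2 SD, and 0.12–0.13 SD for a gap of 0.5 SD.
- Standard error of a difference in means: √(2/30) = 0.26 SD.

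As a share of sampling variance, this is gap² × SD² ÷ (2/30).
- Gap 0.2 SD, 30:30 split: 0.04 × 0.0169 ÷ 0.0667 = 1%.
- Gap 0.5 SD, 30:30 split: 0.25 × 0.0169 ÷ 0.0667 = 6%.
- Gap 0.5 SD, 15:45 split: 0.25 × 0.0127 ÷ 0.0667 = 5%.

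**Step 5. Change from baseline.** The analysis includes baseline as a time level, and the group-by-time term carries the treatment effect. A school gap that stays constant over the three visits cancels from that term. What remains is any difference between schools in how scores change over time. The same formula applies to that difference, with the gap in change in place of the gap in level.

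**The case against.** The strongest reply is that the article does not say that a single sequence ran across both schools. Its wording would also fit separate sequences per school, and a condensed article may leave strata and covariates to a fuller document. This stands as a limit on the wording: one can say that no stratification is described, not that none was done. It does not dispose of the point. The section prints sample blocks and would naturally have named a stratum there. The analysis section lists its factors without school.

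It also stands that effectiveness is a secondary objective of a feasibility trial. The imbalance does not touch the recruitment, attrition or satisfaction criteria. The trial is reported as already conducted, so its allocation can no longer be changed.

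Two stronger readings are tempting.

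- **That school imbalance biases the result.** Under individual randomisation its expectation is zero. In any one trial it is a fixed shift, but over repeated randomisations it is variance that the standard error already reflects.
- **That small blocks in an open-label trial made the next allocation guessable.** The documents do not support this. Recruitment is dated before the trial, and randomisation is undated. If the list was closed before allocation, no one could use a guess to steer entry. Nothing shows that entry was sequential and open to steering.

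**Conclusion.** The point holds as a minor one. As described, school is handled in neither the allocation nor the analysis, and the article contradicts itself on whether schools or teachers were randomised.

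The block scheme favours individual allocation, so a reader should not conclude from the recruitment section alone that arms and schools coincide. Equally, that reading cannot be dismissed until the two sections are reconciled, and it would be far more serious than anything calculated here.

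Given individual, unstratified allocation, the avoidable error is about 1% to 6% of sampling variance, and less for change scores with a stable gap. These sizes rest on assumed school splits, an assumed gap of 0.2 to 0.5 SD and random entry order. None of these is in the article.

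**What to change.** 1. Reconcile Recruitment and Sample Size with Randomization and Blinding. State whether teachers or schools were randomised and, if teachers, whether the sequence was generated within each school.
2. Generate the allocation separately within each school, here if it is still open and otherwise in the follow-on trial. This is a setting in the randomisation tool and leaves the sample size at 60.
3. Report the number of teachers from each school in each arm.
4. Add school and its interaction with time to the group-by-time analysis. The interaction is needed because a school main effect alone does not adjust the group-by-time term. If the analysis has already been run, report this as an adjusted analysis and label it as added.

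Cost with complete data: school takes one between-subject degree of freedom (60 − 2 = 58 falls to 57). School by time takes (2 − 1) × (3 − 1) = 2 within-subject degrees of freedom (58 × 2 = 116 falls to 57 × 2 = 114). If it turns out that each arm was one school, steps 2 and 4 do not apply, and the article should say that effects cannot be separated from school.

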### Assessments Tools

There were 4 points of measurement: screening, baseline, end line, and follow-up. In Table 1, following the SPIRIT 2013 statement [26], an overview of the evaluation instruments used in this study is presented. Both groups received compensation for the time they spent and the internet data they used throughout the baseline, end line, and follow-up periods. The compensation amounts were ~US $3 for baseline, US $7 for the end line, and US$ 10 for follow-up, which is equivalent to the average cost of obtaining internet data in Indonesia. The act of providing monetary compensation as reimbursement is noncontroversial and commonly acknowledged [31].

**Table 1 table1:** Study outcomes and time points of measurement.

Outcome	Instrument	Screening	Baseline	End line	Follow-up
			Day 1	Day 21	Day 41
Sociodemographics (age, education level, sex, marital status, occupation, years as schoolteacher, salary, schoolteacher status)	Demographics	Y^a^	Y	—^b^	—
Source of obtaining BM-MA^c^ information	Demographics	Y	—	—	—
Mental health care service history	Demographics	Y	Y	Y	Y
Smartphone ownership	Demographics	Y	Y	—	—
Internet access	Demographics	Y	Y	—	—
Contact details	Demographics	Y	—	—	—
Convenient contact times	Demographics	Y	—	—	—
Perceived stress	PSS^d^	—	Y	Y	Y
Depression symptoms	GHQ-12^e^	Y	Y	Y	Y
Anxiety symptoms	GAD-7^f^	Y	Y	Y	Y
Well-being	SLS^g^ and SCS-SF^h^	—	Y	Y	Y
Self-efficacy	TSES^i^	—	Y	Y	Y
Mindfulness trait	FFMQ^j^	—	Y	Y	Y
Engagement and experiences with the BM-MA	Questionnaires	—	Y	Y	Y
Qualitative interview of feasibility and acceptability	Interview guideline	—	—	Y	Y

^a^Y: measured.

^b^Not measured.

^c^BM-MA: brief mindfulness–based mobile app.

^d^PSS: Perceived Stress Scale.

^e^GHQ-12: General Health Questionnaire-12.

^f^GAD-7: Generalized Anxiety Disorder.

^g^SLS: Satisfaction With Life Scale.

^h^SCS-SF: Self-Compassion Scale—Short Form.

^i^TSES: Teachers’ Sense of Efficacy Scale.

^j^FFMQ: Five Facet Mindfulness Questionnaire.

#### Sociodemographic and Personal Information

During the screening session, participants’ sociodemographic and personal information was collected using a combination of questions. The open questions inquired about participant age, years as a teacher, and salary, whereas the closed questions required participants to select from a list of options, such as the education level and internet access on a smartphone (yes/no). To ensure participants’ eligibility, sociodemographic and personal data were requested once again at baseline.

#### Measurement of Primary Outcome

The evaluation of the BM-MA implementation in real-world contexts will be the primary outcome for this study. This study will evaluate the adoption of the BM-MA with an engagement and experience questionnaire. On the basis of Howell et al’s [22] findings, a questionnaire will be designed to allow participants to rate their experience using the app.

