At the end of the waiting period, the CG received thorough instructions regarding downloading and using the BM-MA intervention via a smartphone. In the meantime, the BM-MA group was instructed to complete questionnaires at baseline, postintervention, and at 1-month follow-up of the BM-MA intervention. After the baseline measures were completed, participants in the BM-MA group were provided with an access code and details of how to download the BM-MA to their smartphone. During the 21-day study period, they were urged to use the app daily. At baseline, postintervention, and at 1 month follow up of the BM-MA intervention, both groups were invited to attend a Zoom session to finish the measurements in real time, monitored by random assignments. Both groups were reminded about their right to withdraw from the study at any moment if they so chose. The follow-up evaluation was conducted 1 month postintervention for both groups. The intervention tries to ensure that no participant will face stigma as a result of participation by removing any potentially objectionable language according to the feedback from the local government partner, the Dinas Pendidikan Kepemudaan dan Olahraga Provinsi (Province Youth and Sports Office). The overview of the BM-MA pilot RCT study design following CONSORT guidelines is presented in Multimedia Appendix 1.

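### Adoption, the primary outcome, is judged by self-rating while the app's practice tracker is used nowhere, and Table 1 schedules that rating at Day 1, before anyone has the app

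*Protocol article*

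**What the plan says.** Under Measurement of Primary Outcome the article states: "The evaluation of the BM-MA implementation in real-world contexts will be the primary outcome for this study". The instrument follows: "This study will evaluate the adoption of the BM-MA with an engagement and experience questionnaire". Its purpose is described in these terms: "a questionnaire will be designed to allow participants to rate their experience using the app".

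Study Objectives asks, among other things, whether the app could be used in the intended way during the study and whether its implementation could be kept up to the end. The Abstract gives the intended amount as 10-20 minutes a day for 3 weeks, and the Intervention section repeats the daily figure. That section also describes an app feature with which participants can "track the overall duration and frequency of practice over a period of 21 days".

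In Table 1 (Assessments Tools) the row "Engagement and experiences with the BM-MA" is marked as measured at baseline (Day 1), end line (Day 21) and follow-up (Day 41), with no split by arm. Overview of Study Design says when each arm receives the app. For the intervention arm: "After the baseline measures were completed, participants in the BM-MA group were provided with an access code". Controls were "asked to answer questionnaires at baseline, postintervention, and at 1-month follow-up before being allowed access to the BM-MA intervention".

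The one analysis of engagement, in Data Analyses, asks "whether the subjective ratings of involvement and experience with the BM-MA by participants correlate with any potential improvements" in well-being in the BM-MA group.

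**The concern.** Whether an app was used as intended is a question about behaviour, and the article supplies a yardstick for it in minutes per day. The primary outcome is instead tied to how participants rate their experience. Someone may think well of an app and rarely open it, or stop after a few days and still answer favourably at Day 21.

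The Discussion says the findings will decide whether the BM-MA goes forward to efficacy testing. A favourable rating reported as adoption could carry that decision although little practice took place. A larger trial would then be planned without knowing how much practice to expect.

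The schedule adds a smaller, definite fault: a rating of engagement with the app is due on a day when nobody has had the app.

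The correlation analysis inherits the weakness. Both of its variables are self-reports by the same people, so general response style, or goodwill in those who feel better, can produce an association without any contribution from practice.

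**Working it through.** The article gives no figure for adoption to reproduce. The check sets its sections side by side and adds simple counts.

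**1. The intended amount.** Inputs: 10-20 minutes a day (Abstract, Intervention) and 21 days (Overview of Study Design, Intervention).
- Lower end: 10 × 21 = 210 minutes.
- Upper end: 20 × 21 = 420 minutes.

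As an illustration that is not in the article, take a participant who meets the target for 7 days and then stops. The total is 7 × 10 = 70 to 7 × 20 = 140 minutes, and 70/210 = 140/420 = 33% of the intended amount. A rating of experience need not reveal this; a count of days and minutes would.

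**2. Where practice is measured.**
- Primary outcome: the engagement and experience questionnaire only.
- Table 1: questionnaires and interviews; no entry for days, sessions or minutes of app use.
- Acceptability and Feasibility: the CSQ-8 (more than 70% of participants scoring 24 or above), structured interviews, ease of recruitment, enrollment rate, attrition rate, and undefined app scores.
- Data Analyses: subjective ratings correlated with improvement.

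The tracker appears only in the Intervention section. The CSQ-8 and interviews are self-report. Attrition is not defined as stopping practice, and the compensation (about US $3, $7 and $10) is set by assessment point, so a participant can complete the study after giving up the app.

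**3. Table 1 against access to the app.** Inputs: 30 per arm, three time points, no attrition assumed.
- Day 1: 0 of 60 participants have the app, because the BM-MA arm receives its code after baseline and controls receive access after follow-up.
- Row applied to both arms, as printed: 60 × 3 = 180 questionnaires. Those from people who have had access: 30 × 2 = 60 (33%). The other 120 (67%) come before access.
- Row applied to BM-MA only: 30 × 3 = 90 questionnaires, of which 30 (33%) come before access.

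These counts show the extent of the schedule conflict. The article does not state them.

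**The case against.** Several points on the other side have weight.

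- **The timing fault is limited.** A reader might infer from Table 1 that the primary measure as a whole precedes the app. It does not: Day 21 and Day 41 are sound for the BM-MA arm, and nothing says that the Day 1 value is analysed. This stands.
- **The tracker is described as a tool for participants.** The article does not say that investigators hold or can export its record. It would be wrong to conclude that retrievable usage data were ignored. This stands, and the fix has to be conditional.
- **The questionnaire is not shown.** It may ask about frequency or minutes, and an article commonly leaves item content to the full protocol. So one cannot say that it is unable to capture practice. Any such item would still be self-report, and the stated aim is to rate experience.
- **Its wording is in the future tense.** A reader might infer that the instrument did not exist when the trial ran. The article mixes tenses throughout, so this is not established.
- **Other feasibility measures exist.** Attrition can speak to whether the programme was continued, if that question means retention. None of these measures quantifies practice, so the gap remains.
- **The correlation is openly called subjective.** The article makes no causal claim and does not say how improvement is calculated, so a complaint about unadjusted change scores has no basis in the text. Low power with 30 participants is not the argument either: a small sample brings imprecision, while a shared source of error would persist at any size.
- **The trial is over.** The Results section reports conduct from January through March 2024 and analysis from March through May 2024. A change of measure now may be post hoc and must be labelled so.

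**Conclusion.** The point holds with these limits. The article ties its primary outcome to a self-rating, asks whether the app was used as intended, states the intended amount (210-420 minutes over 21 days), describes a feature that tracks duration and frequency, and then uses that feature in no outcome, schedule, criterion or analysis. As written, the primary outcome does not give an objective answer to the question about intended use.

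The Day 1 entry in Table 1 contradicts the account of when access was given. It affects 30 of 90 questionnaires if only the BM-MA arm answers, or 120 of 180 lack prior access if both arms answer as printed. Both counts assume no attrition.

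The documents do not show that adoption was in fact poor, that a retrievable log was discarded, or that the Day 21 and Day 41 ratings are invalid for the BM-MA arm. How much the choice of measure matters depends on how far ratings and practice diverged, which the article cannot tell us.

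**What to change.** 1. **State whether the tracker record can be retrieved.** If it can, report for all 30 participants randomised to BM-MA the number of the 21 days on which the protocol's own daily target was logged, and total minutes, counting those who never downloaded the app as zero. Present this as the objective adoption measure beside the questionnaire. Label it, and any cut-off for use as intended, as post hoc if it was not fixed before the data were seen.
2. **If the record cannot be retrieved,** say so, and do not present the experience rating as evidence that the app was used as intended.
3. **Correct Table 1.** Remove the Day 1 entry for engagement and experiences, and limit the row to the BM-MA arm.
4. **Label the engagement correlation exploratory,** noting that both variables are self-report from the same people. Where logs exist, use logged minutes in place of the rating. This reduces the shared-rater problem, but the amount practised remains the participant's own choice.

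The cost is a data export, if one is possible, and changes of wording. The downsides are small: practice outside the app is not counted, and the usage analysis may have to carry a post hoc label.
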